### Intervention

#### Dementia Care Mapping (DCM™)

DCM™ will be implemented according the standard procedures identified in the DCM™ 8 User’s Manual [26]. The intervention comprises training two care home staff in use of DCM™ followed by implementation of three full mapping cycles. Two eligible staff members will be identified as mappers in all homes prior to randomisation and will be consented at baseline. After completion of the standard 4-day DCM™ training course, the mappers will run briefing sessions 1–2 weeks prior to undertaking the mapping observations. During the briefing session, mappers will consult with staff about selection of appropriate residents to be mapped. Residents chosen for inclusion in mapping observations do not have to be trial participants and verbal consent from residents to be observed will be gained by the mappers ahead of mapping observations commencing. Mapping involves the mappers continuously observing between two and five people with dementia, over a period of four to six consecutive hours, in communal living areas only. The mappers will then analyse the data they collect and present it in a report that will be fed back to the staff team. During the feedback session, an action plan will be produced in collaboration with the staff team, which will detail areas that the home aims to improve, based on the DCM™ data. Progress on these actions is monitored during the next mapping cycle. The first cycle should be completed by approximately 3 months post randomisation and the second and third cycles at approximately 8 months and 13 months post randomisation, respectively. An expert mapper, who is a practitioner experienced in the implementation of DCM™, will provide support to each care home during completion of their first cycle of mapping in order to maximise intervention fidelity across all homes. Telephone/email support for DCM™ implementation will be available to all care homes thereafter through the DCM™ lead for the trial, if required. Mappers will be asked to complete and return data on mapping practice for all three mapping cycles including: information on numbers of staff in the care home receiving DCM™ briefing; number of hours of mapping; number of residents mapped; number of staff attending feedback sessions and number of action plans developed. Mappers will be provided with a standard reporting template to gather this information.

#### Usual Care

UC is defined as normal care delivered within the setting (as measured by training audit, a bespoke UC Questionnaire and the Care Home Context and Organisational Questionnaire). No restrictions will be imposed on current practices or on homes undertaking additional development or training as part of UC, with the exception of control arm homes being required not to implement DCM™ during their trial involvement period. Person-centred care is considered best practice within dementia care [13] and as such care homes are expected to provide staff with appropriate training to deliver care of this type [47].

### Registration and randomisation

Residents will be registered centrally with the Clinical Trials Research Unit (CTRU) at the University of Leeds after care home recruitment, the care home training audit, confirmation of eligibility, informed consent and collection of resident baseline data.

Once all residents within a care home have been registered, care homes will be randomised centrally at the CTRU to receive DCM™ + UC or UC, leading to two sources of clustering: cluster-randomisation and DCM™ treatment provision. The former occurs at randomisation (care homes are nested within treatment arms), the latter afterwards (care homes are partially nested within arms) so we anticipated that the clustering effect will vary across arms, and assumed a higher design effect in the intervention arm. Care homes will be randomised on a 3:2 basis. A computer-generated minimisation programme incorporating a random element will be used to ensure treatment arms are balanced for the following care home characteristics: (1) home/unit type (general residential/nursing, specialise in dementia care), (2) size (large at least 40, medium/small fewer than 40), and (3) provision of dementia awareness training by research team (yes, no), (4) recruitment hub (West Yorkshire, Oxfordshire, London). The latter was changed from prior use of DCM™ in the last 5 years as balancing the intervention across recruitment hubs was considered more important. Following randomisation, a member of the research team will inform the care home manager of their allocation and for those homes allocated to DCM™ + UC, the staff consented to take on the role of mappers will also be informed, so arrangements for attendance at DCM™ training can be made.

### Data assessments

Assessments will be undertaken at screening (prior to consent); baseline (prior to resident registration); 6 months post randomisation and 16 months post randomisation. Baseline data collection visits will be conducted over approximately 3 weeks in each home and follow-up visits over a 1–2-week period. Required data, assessment tools, collection time points and processes are summarised in Table 1.

**Table 1 Tab1:** Summary of assessments

Assessment	Type	Method of completion	Timeline			
			Screening	Baseline	6 months	16 months
Care home eligibility	CRF	Researcher assessment	X			
Training review	CRF	Researcher assessment	X			
Dementia awareness training	CRF	Dementia awareness trainer	X			
Resident screening (demographics)	CRF	Researcher assessment	X			
Staff mapper screening	CRF	Researcher assessment	X			
Consent (staff mapper, resident (includes personal/nominated consultee), staff proxy informant, RF proxy informant)	Consent Form	Self-completion (witnessed)	X			X
Participant eligibility (staff mapper, resident, staff proxy informant, RF proxy informant)	CRF	Researcher assessment	X			X
Participant contact details (resident, staff proxy informant, RF proxy informant)	CRF	Researcher assessment	X			X
Cohen-Mansfield Agitation Index (CMAI) abridged	Questionnaire booklet	Independent researcher observations (R)		X	X	X
Pittsburgh Agitation Scale (PAS)	Questionnaire booklet	Independent researcher observations (R)		X	X	X
Care home manager demographics	Questionnaire booklet	Researcher interview (CM)		X	X	X
Care home demographics	Questionnaire booklet	Researcher interview (CM)		X	X	X
Group Living Home Characteristics (GLHC)	Questionnaire booklet	Researcher assessment (CH)		X	X	X
Environmental Audit Tool (EAT)	Questionnaire booklet	Researcher observations (CH)		X	X	X
Quality of Interactions Schedule (QUIS)	Questionnaire booklet	Researcher observations (R/S)		X	X	X
Staff proxy informant demographics	Questionnaire booklet	Researcher interview (SP)		X	X	X
Resident demographics	Questionnaire booklet	Researcher assessment		X	X	X
RF proxy informant demographics	Questionnaire booklet	Researcher interview (RF)		X	X	X
Cohen-Mansfield Agitation Index (CMAI)	Questionnaire booklet	Researcher interview (SP)		X	X	X
Neuropsychiatric Inventory (NPI-NH)	Questionnaire booklet	Researcher interview (SP)		X	X	X
Functional Assessment Staging (FAST)	Questionnaire booklet	Researcher interview (SP)		X	X	X
Clinical Dementia Rating (CDR)	Questionnaire booklet	Researcher interview (SP)		X	X	X
DEMQOL-Proxy	Questionnaire booklet	Researcher interview (SP/RF)		X	X	X^a^
EQ-5D-5 L	Questionnaire booklet	Researcher interview (SP/RF/R)		X	X	X^a^
QUALID	Questionnaire booklet	Researcher interview (SP/RF)		X	X	X^a^
QOL-AD	Questionnaire booklet	Researcher interview (R)		X	X	X
Resident comorbidities	Questionnaire booklet	Researcher assessment		X	X	X
Health care resource use	Questionnaire booklet	Researcher assessment		X	X	X
Prescription medications	CRF	Researcher assessment		X	X	X
Resident registration	Questionnaire booklet	Researcher assessment		X		X
Staff booklet	Questionnaire booklet	Self-completed (S)		X	X	X
General Health Questionnaire (GHQ-12)	Questionnaire booklet	Self-completed (S)		X	X	
Sense of Competence in Dementia care Staff (SCIDS) scale	Questionnaire booklet	Self-completed (S)		X	X	X
Safety reporting	CRF	Researcher assessment		Monthly following randomisation		
RUSAE Report	CRF	Researcher assessment		As highlighted.		
			Mapper training	Cycle 1	Cycle 2	Cycle 3
Mapper training	CRF	DCM™ trainer	X			
DCM™ adherence	Questionnaire booklet/CRF	DCM™ expert/ independent reviewer		X	X	X
DCM™ briefing summary	CRF	CH mapper		X	X	X
DCM™ feedback summary	CRF	CH mapper		X	X	X

Key: *CRF* Case Report Form, *CH* care home observations, *CM* care home manager, *DEMQOL-Proxy* Dementia Quality of Life measure – proxy version, *EQ-5D-5 L* EuroQol five dimensions, five levels, *QUALID* Quality of Life in Late-Stage Dementia, *QOL-AD* Quality of Life in Alzheimer’s disease measure, *R* resident, *RF* relative/friend proxy informant, *RUSAE* Related Unexpected Serious Adverse Event, *S* staff, *SP* staff proxy informant, X^a^ – only for relative/friend informants consented at baseline and still meeting eligibility criteria

### Outcomes

The primary outcome is agitation at 16 months following randomisation. The primary measure of agitation is the Cohen-Mansfield Agitation Inventory (CMAI) [48] rated by a staff member who knows the resident well. The Pittsburgh Agitation Scale (PAS) [49] and an adapted CMAI (see below), rated by an independent researcher not involved in any other data collection within that care home and blinded to allocation, will provide concurrent validity. This addresses the issue of potential bias of staff responses, based on the inability to blind them to allocation status.

There are a number of secondary outcomes each relating to residents, staff or care homes. Secondary outcomes at 6 and 16 months post randomisation relating to residents are: Neuropsychiatric Inventory (NPI) [50]; DEMQOL-Proxy, Quality of Life in Late Stage Dementia (QUALID) [51]; QOL-AD [52], EuroQol five dimensions, five levels (EQ-5D-5 L) [53]; the prescription and use of psychotropics, memantine, benzodiazepines and anti-depressants; and, safety reporting (serious adverse events (SAEs)). Secondary endpoints at 6 and 16 months post randomisation relating to staff are: General Health Questionnaire (GHQ-12) [54] and Sense of Competence in Dementia care Staff (SCIDS) scale [55]. Secondary endpoints relating to homes are: intervention fidelity (at 16 months) and Quality of Interactions Schedule (QUIS) [56] at 6 and 16 months.

### Outcome measures

#### Resident-related outcome measures

##### Agitation

**Cohen-Mansfield Agitation Inventory (CMAI)** [6, 48]:

The CMAI measures 29 agitated or aggressive behaviours [57] on frequency, using a seven-point scale (1–7) ranging from ‘never’ to ‘several times an hour’ based on behaviours over the previous 2 weeks. A total score is obtained by summing the 29 individual frequency scores (range 29–203). It has good psychometric properties [58] including construct validity and factor structure [59], concurrent validity [60] reliability [61] and test-retest reliability [62] in care home settings. There are also available data on expected change in points from previous similar studies supporting the sample size calculation. The CMAI will be completed in accordance with the *CMAI Manual* [48] via staff proxy report in the context of an interview with a trained researcher.

**Pittsburgh Agitation Scale** [49]:

The PAS is an observational rating of the presence and intensity of agitation within four behaviour groups, which has good reported reliability and validity [49]. Observations are conducted for between 1 and 8 h. In this trial, data collection will be undertaken by an independent researcher using a standardised observation period (between 10.00 and 17.00 hours), on consented residents within communal areas.

**Adapted CMAI** [48]:

The adapted CMAI is a researcher-completed, direct observational tool, which records observed levels of agitation over a single observation period, on a single day. It was adapted specifically for the purpose of this trial since the original CMAI scale considers proxy reported behaviours over the previous 2 weeks and is not suitable for direct observational use on a single day. Adaption included changing the CMAI’s seven-point scale related to the previous 2 weeks to a four-point scale (‘never’ to ‘several times an hour’) appropriate for observations on a single day. In this trial, data collection will be standardised to observations of consented residents within communal areas between 10.00 and 17.00 hours.

##### Behaviours that staff may find challenging to support

**Neuropsychiatric Inventory-Nursing Home (NPI-NH)** [50]:

The NPI-NH is a validated 12-item measure with good reported reliability, that records a range of BSC including, delusions, hallucinations, agitation/aggression, depression/dysphoria, anxiety, elation/euphoria, apathy/indifference, disinhibition, irritability/lability, aberrant motor behaviour, sleep and night-time behaviour disorders and appetite/eating disorders [50]. It will be completed via staff proxy report in the context of an interview with a trained researcher.

Quality of life

Multiple quality of life measures have been implemented since no one measure was identified that could provide the required sensitivity to quality of life in this participant group, and which could facilitate participant self-report in those with severe dementia.

**DEMQOL-Proxy** [63]:

The DEMQOL-Proxy is a quality of life measure with 32 items covering mood, behavioural symptoms, cognition and memory, physical and social functioning and general health that are administered by an interviewer. It is completed by a carer of the person with dementia and administered by an interviewer. It has acceptable psychometric properties for measuring quality of life in dementia [64] and has been valued to enable the derivation of preference based indices (utility values) [65] and will thus be employed in the secondary cost-utility analyses. It will be completed via staff proxy report in the context of an interview with a trained researcher. The relative/friend proxy will also complete the DEMQOL-Proxy where available to provide complimentary additional data.

**EQ-5D-5 L/EQ-5D-5 L Proxy** [53]:

EQ-5D is a standardised measure of health outcome that provides a single index value for health status [66, 67]. It has five items covering: usual activities, self-care, mobility, pain and anxiety/depression, each with five response options (no problems, slight problems, moderate problems, severe problems and unable to do task). It will be completed via staff proxy report in the context of an interview with a trained researcher. The resident will complete the EQ-5D-5 L when able via interview with the researcher and the relative/friend proxy, where recruited, will complete the EQ-5D-5 L Proxy to provide complimentary additional data.

**Quality of Life in Late Stage Dementia (QUALID) [**51**]:**

The QUALID is an 11-item proxy completed scale that rates the presence and frequency of quality of life-related behaviours over the previous 7 days. It is reliable and valid for rating quality of life in people with moderate to severe dementia and has good internal consistency, test-retest reliability and inter-rater reliability. It will be completed via staff proxy report in the context of an interview with a trained researcher. The relative/friend proxy will also complete the QUALID where available to provide complimentary additional data.

**QOL-AD** [68]:

The QOL-AD is a 13-item self-report questionnaire. It has good reported internal reliability, test-retest reliability and convergent validity [68]. It is reported to be reliable for use with people with mild to moderate dementia (11 or greater on the MMSE [69] and more severe dementia (MMSE of >2)) [70, 71]. It will be completed by the resident in the context of an interview with a trained researcher.

##### Use of health care services

Health care resource use measure:

This measure is adapted from one that has recently been piloted in a care home feasibility trial [72]. It captures primary (e.g. general practitioner and nurse visits) and secondary (Accident and Emergency Department and other hospital visits) health care usage. This will be completed by the researcher from care home records.

##### Dementia severity

**Clinical Dementia Rating Scale (CDR)** [73]:

The CDR is a standardised scale for rating the severity of dementia from no cognitive impairment to severe or advanced dementia [74] and is completed by a trained assessor via informal interview/conversation with the person or a proxy. It will be completed by the researcher in discussion with the staff proxy.

**Functional Assessment Staging in Alzheimer’s Disease (FAST)** [42]:

The FAST is a scale designed to capture the functional severity of dementia. It is particularly designed for use in more moderate to severe dementia. It is completed by proxy report from a caregiver. This will be completed by the researcher with information from a staff informant.

#### Staff-related outcome measures

Staff measures are distributed by the researcher or care home manager and returned in a sealed envelope either directly to the researcher or posted into a secure locked box located within the care home during data collection visits. Alternatively, staff may return the measures direct to the CTRU using a pre-paid envelope.

##### Work stress

**General Health Questionnaire 12-item (GHQ-12)** [54]:

The GHQ-12 is a measure of stress/psychological well-being and is used with the general population. It has good reported psychometric properties [75].

##### Job or role efficacy

**Sense of Competence in Dementia care Staff (SCIDS) scale** [55]:

The SCIDS is a self-complete 17-item scale that measures staffs’ sense of their own competence with regard to delivery of dementia care across four sub-scales (professionalism, building relationships, care challenges, sustaining personhood). It has acceptable internal consistency and test-retest reliability [55].

#### Care home-related outcome measures

##### Care quality

**Quality of Interactions Schedule (QUIS)** [56]:

The QUIS is an observational measure of the quality of interactions between staff and people with dementia, which has reported adequate inter-rater reliability and sensitivity [76]. The QUIS is administered via researcher observations, using a time-sampling approach [56, 77]. Data are amalgamated to provide a rating of the quality and quantity of interactions at the care home. In this trial, observations will be undertaken by a researcher for 15-minute periods, in communal areas in the care home, during two 2-h observations (one a.m. and one p.m.) during a 7-day period.

##### Care home environment, context and organisation

**Environmental Audit Tool (EAT)** [78]:

The EAT is a valid and reliable instrument that can be used to differentiate between the quality of environmental design in various types of dementia care facilities [78]. It is completed by the researcher through observation and with information from a senior staff member.

Care home context and organisational questionnaire

Information about the care home context and organisation will be gathered using a specially designed questionnaire asking questions about the home (size, type, ownership, geography, staff turnover, staff ratios, resident demographics, etc.), manager (qualifications, length of time in post, leadership style, etc.) and staff (qualifications, length of time in post, English as first language, etc.) demographics. It is completed by the researcher with information from a senior staff member.

**Group Living Home Characteristics Questionnaire (GLHC)** [79]:

This is a measure of the style of care being delivered in the home. It examines how ‘home-like’ the care delivered is. It is completed by the researcher with information from a senior staff member.

### Bias and blinding

Due to the nature of the intervention, it will not be possible to blind care homes or staff to the allocation status. To minimise the potential for bias, the trained mappers will not be involved in providing any outcome data. To ensure consistency, where possible the same staff member will be asked to complete resident measures at each data collection point. All data will be gathered by trained researchers in discussion with the informant with the exception of the staff measures questionnaires, which will be completed independently by staff. To ensure reliability and to restrict the potential for researcher bias, intra-rater reliability will be achieved for all researchers at training. Effort will be made to blind all trial researchers to allocation status. The researcher conducting the observations for the PAS and abridged CMAI will be independent and will remain blind. Any unblinding will be recorded and unblinded researchers will not conduct any further follow-up data collection in those care homes.

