### Statistical analysis

A single final analysis is planned when all follow-up data have been collected and the primary analyses will be carried out on an intention-to-treat basis, utilising all available follow-up data, comparing treatments as allocated.

It is expected that a sizeable proportion of residents will be missing from the main analyses, and that missing data can be predicted by known variables, hence the principal method for handling missing scale data will be multiple imputation under the Missing at Random (MAR) assumption. Sensitivity analyses will be carried out to assess the impact of the choice of imputation model and of assuming data are Missing Not at Random (MNAR) as appropriate.

The impact of cluster randomisation is expected to be equal across arms but that of treatment provision is not. As such, the principal method for handling clustering effects will be to fit a multilevel model that allows care home- and resident-level variances to differ across arms. A sensitivity analysis will be conducted fitting a random intercept model assuming equal total variances. The resident-level primary outcome of agitation (continuous CMAI score) will be analysed at 16 months post randomisation using a linear two-level heteroscedastic regression model [70], adjusting for design factors, with a contrast for intervention and control. The model will be adjusted for the following fixed effects: care home (level 2) covariates (home type and size, provision of dementia awareness training and hub) and resident (level 1) covariates (severity of dementia, age and baseline CMAI score). Unadjusted and adjusted ICCs, treatment effect estimates and corresponding 95 % confidence intervals will be presented.

For residents where a PAS and an abridged CMAI score are also available, a sensitivity analysis will be conducted replacing the CMAI score in the primary analysis with the PAS and abridged CMAI scores looking for consistency in the size and direction of effect.

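### Researchers are trained to intra-rater reliability, which cannot show that different researchers score alike; PAS, adapted CMAI and QUIS need an inter-rater standard.

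*Protocol article*

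**What the plan says.** The reliability standard for the trial's researchers is in Bias and blinding: "To ensure reliability and to restrict the potential for researcher bias, intra-rater reliability will be achieved for all researchers at training".

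Three sets of scores depend directly on a researcher's observation:

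- **PAS and adapted (abridged) CMAI.** Under Outcomes these are "rated by an independent researcher not involved in any other data collection within that care home and blinded to allocation". Their purpose is given there too: "This addresses the issue of potential bias of staff responses, based on the inability to blind them to allocation status". Statistical analysis uses them in a sensitivity analysis, "replacing the CMAI score in the primary analysis with the PAS and abridged CMAI scores looking for consistency in the size and direction of effect".
- **QUIS.** This is observed by a researcher in communal areas. It is the only measure listed under Care quality.

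On reliability of the instruments, the QUIS is described as one "which has reported adequate inter-rater reliability and sensitivity", and the PAS is credited with good published reliability. For the adapted CMAI the Agitation section says "It was adapted specifically for the purpose of this trial" and reports no reliability.

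On continuity of raters, Bias and blinding adds: "Any unblinding will be recorded and unblinded researchers will not conduct any further follow-up data collection in those care homes".

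**The concern.** Intra-rater reliability is agreement of one rater with themselves. A researcher who always scores high, or always low, passes it. The sentence gives its purpose as securing reliability and limiting researcher bias across all researchers, and self-consistency does not serve that purpose when several researchers score different homes.

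What is at stake is the blinded check. The primary CMAI comes from staff who know the allocation. The article's answer is to put PAS and adapted CMAI scores through the primary model and see whether the effect has similar size and direction. If observers differ in severity, that comparison is noisier and harder to read, and agreement or disagreement with the staff CMAI says less. QUIS, as the care-quality measure, is exposed in the same way.

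**Working it through.** **1. Is agreement between this trial's researchers set anywhere else?**

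- Bias and blinding: intra-rater only, at training.
- Care quality (QUIS): inter-rater reliability is mentioned, but as a published property of the instrument, not a standard for these researchers.
- Agitation (PAS): published reliability of the instrument only.
- Agitation (adapted CMAI): none stated. The scale was changed from seven points over two weeks to four points on a single day, so rater training is the only reliability safeguard that the article gives for it.

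No section supplies the missing standard.

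**2. The plan's own figures (Sample size).** Inputs: 50 homes at 3:2 (30 and 20), 15 residents each, 25% loss, 11 analysed per home, ICC 0.10, difference 3, SD 7.5, two-sided 5%.

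- Design effect = 1 + (11 − 1) × 0.10 = 2.0, as stated.
- Effective numbers: 30 × 11 / 2.0 = 165 and 20 × 11 / 2.0 = 110.
- SE = 7.5 × √(1/165 + 1/110) = 0.923; 3 / 0.923 = 3.25; 3.25 − 1.96 = 1.29; power about 90.1%, against 90% stated.

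These figures reproduce and are not in dispute. They serve only as a base for step 3.

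**3. What rater differences would cost (illustration).** The article gives no between-rater variance, so the rise in ICC is assumed. If one observer scores all residents in a home and observers differ between homes, rater variance behaves as home-level variance. With total variance held fixed, the standard error is proportional to the square root of the design effect.

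| ICC | Design effect, 1 + 10 × ICC | SE relative to ICC 0.10 |
|---|---|---|
| 0.10 | 2.0 | 1 |
| 0.15 | 2.5 | √(2.5/2.0) = 1.118 (+12%) |
| 0.20 | 3.0 | √(3.0/2.0) = 1.225 (+22%) |

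**4. Cross-check with rater variance added on top.** If raters add a share r of the existing total variance, ICC = (0.10 + r)/(1 + r) and the contrast's variance scales with (1 + r) × design effect.

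- r = 0.05: ICC 0.143, design effect 2.43, √(1.05 × 2.43 / 2.0) = 1.13.
- r = 0.10: ICC 0.182, design effect 2.82, √(1.10 × 2.82 / 2.0) = 1.25.

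The size is similar. If an observer-rated scale carried the same effect of 3/7.5 = 0.4 SD, power would fall from 90% to about 82% or 74%. The article sets no power target for these scales, so this is a gauge only.

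**5. Reach of the illustration.** The ICC of 0.10 and the 11 residents per home are planning values for the staff-rated CMAI, borrowed here for PAS and adapted CMAI. QUIS is amalgamated to home level, so the residents-per-home formula does not apply to it. There, rater variance adds directly to the variance of the home scores, by an amount that the article does not allow one to calculate.

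**The case against.** **A slip of the pen.** The stated purpose and the reference to all researchers both suggest that *inter-rater* was meant. That is quite possible, and the article cannot show how training was actually run. But nothing in it corrects the word, and the standard as written is the one researchers would be held to.

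**Detail belongs in the full protocol.** Thresholds, training material and certification of replacements are commonly left to the full protocol or a training manual, and their absence from an article is no fault. This stands. The point rests only on the standard that the article does state, which does not do its stated job.

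**The trial has protections.** This also stands, and it limits the consequence. Homes are randomised after baseline. The observer for the blinded scales is independent of other data collection in the home, and the article commits to this: "The researcher conducting the observations for the PAS and abridged CMAI will be independent and will remain blind". Hub is both a minimisation factor and a fixed effect in the model, so rater differences between hubs are balanced and adjusted for. Home-level variance is modelled and may differ by arm, so rater differences nested in homes enter the standard error.

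**A stronger reading.** A reader might infer that the rule on unblinded researchers biases the comparison of arms: more unblinding in intervention homes, hence more replaced raters there, hence a spurious difference. For example, replacement in 40% of intervention and 10% of control homes, with replacements scoring 0.3 SD apart, would give (0.40 − 0.10) × 0.3 = 0.09 SD. The documents support none of these inputs. They do not say that unblinding is more frequent in one arm, and the sum needs every replacement to err in the same direction. If replacements are as likely to be lenient as severe, the expected arm difference is zero and only variance is added. The route is more plausible for QUIS, whose researchers have only an effort at blinding, but it is not shown there either.

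**Conclusion.** The point holds as a flaw in a stated rule. Intra-rater reliability does not limit differences between researchers, and no other text sets agreement between them. The supported consequence is lost precision and weaker interpretability of PAS, adapted CMAI and QUIS, and so of the blinded sensitivity analysis. For PAS and adapted CMAI the standard error would grow by about 12% or 22% if rater differences raised the ICC to 0.15 or 0.20. That assumes one observer per home, 11 residents per home and a base ICC of 0.10; the rise itself is assumed.

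A difference between arms remains a possibility where raters change after unblinding, but it is not demonstrated. The primary CMAI is a staff-proxy report, so it, the primary model and the sample size are unaffected.

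**What to change.** In Bias and blinding, replace *intra-rater* with *inter-rater*. Require every researcher who scores PAS, adapted CMAI or QUIS to reach a pre-set agreement on a common set of training observations before first use (for example, an ICC or weighted kappa of at least 0.7). Apply the same check to any replacement before they collect follow-up data. Record who rated each assessment, so that the spread of raters over homes and arms can be reported. The threshold and material can sit in the full protocol or training manual.

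The cost is a wording change and common scored material within the existing training; some researchers may need a repeat session. No sample-size figure changes. The Trial status section says that recruitment is still under way, so remaining assessments can benefit.
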